**Data management**

Participants will be anonymised and identified via assigned study ID. No participant’s identification will appear in data record form (DRF). Research assistants will record participant’s data in DRF. A principal researcher will check for DRF completeness before database entry. Paper documents will be kept in a safe locked cabinet and will be destroyed after 5 years.

**Sample size estimation**

The Park et al’s study^3^ has indicated that rates of PEP in aggressive and standard volume intravenous fluid was 3% and 11.6%, respectively. Based on these findings, 286 participants would be enrolled for the current study given alpha-error, power, and allocation ratio of 5%, 20%, and 1:1, respectively. To compensate for enrolment error that might occur, 300 participants will be recruited.

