**Randomisation and concealment**

A permuted block randomisation with varying block size (4-8 participants per block), 1:1 allocation ratio, will be used to generate random sequence list. This sequence will be concealed with sequentially numbered, opaque, sealed envelopes, which will be revealed during admission at 1 day before ERCP. Random sequence list and envelopes will be prepared by statisticians who will not involve in this study.

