**Statistical analysis**

Descriptive statistics will be conducted to describe data characteristics. Continuous data will be described with mean and standard deviation (SD) or median and interquartile range (IQR) depended on whether their distribution is normal or not. Categorical data will be described with percentage.

Comparison between groups will be performed by statistical test as follows: the chi-square or Fischer’s exact tests for categorical data (e.g. the outcome data), and the independent student t- or Mann-Whitney U tests for continuous data (normal and non-normal distribution, respectively). Risk ratios and their 95% confidence intervals, representing the strength of association between the factors of interest and the outcomes, will be estimated. A P-value of ≤ 0.05 will be considened as statistical significance.

Subgroup analysis will be conducted for naïve ampulla participants and participants who undergo high-risk procedures defined by pancreatic duct wiring, pancreatic duct injection, precut sphincterotomy, and balloon dilation of the ampulla.

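### The protocol states 20% power, but its 286 participants are the number for 80% power: the type II error has been written where power is named

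*Protocol*

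**What the plan says.** The Sample size estimation section takes its rates from an earlier randomised trial of aggressive hydration, reporting that "rates of PEP in aggressive and standard volume intravenous fluid was 3% and 11.6%, respectively". From these it concludes that "286 participants would be enrolled for the current study given alpha-error, power, and allocation ratio of 5%, 20%, and 1:1, respectively". It then adds a margin: "To compensate for enrolment error that might occur, 300 participants will be recruited".

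The section does not say whether the 5% is one- or two-sided, or which test the calculation assumes. The Statistical analysis section allows either the chi-square or Fisher's exact test for the outcome data and sets only a threshold: "A P-value of ≤ 0.05 will be considened as statistical significance". The Randomisation and concealment section confirms 1:1 allocation. Neither power nor beta appears anywhere else in the protocol.

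**The concern.** The three parameters and three values are listed in matching order, so the sentence assigns 20% to power. A trial with 20% power would have an 80% chance of missing the effect it was designed to find. That is not a credible design for a confirmatory comparison, and it does not fit a total of 286.

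This is the protocol's only statement of power for the primary outcome. If it is wrong, the prespecified record misdescribes the design, and anyone recomputing the sample size from the stated inputs will get a very different number. The missing sidedness and test make it harder to see which input is at fault.

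**Working it through.** **Inputs**

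- Intervention rate p1 = 0.03 and control rate p2 = 0.116 (Sample size estimation). Difference = 0.086; mean rate = (0.03 + 0.116)/2 = 0.073.
- Alpha = 0.05 (Sample size estimation). Two-sided is an assumption, giving z = 1.96; one-sided is also tried below.
- Allocation 1:1 (Sample size estimation; Randomisation and concealment).
- Power = 20% as written, so z = −0.8416; or 80% if the 20% is beta, so z = +0.8416.

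**Formula** (two proportions, pooled variance under the null, no continuity correction)

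n per arm = [1.96·√(2·0.073·0.927) + z_power·√(0.03·0.97 + 0.116·0.884)]² / 0.086²

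The two square roots are √0.135342 = 0.3679 and √0.131644 = 0.3628, and 0.086² = 0.007396.

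**Reproducing 286 (power 80%)**

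(1.96·0.3679 + 0.8416·0.3628)² / 0.007396 = (0.7211 + 0.3054)² / 0.007396 = 142.4, rounded up to 143 per arm, **286 in total**. This matches the protocol exactly.

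**Power 20% as written**

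(0.7211 − 0.3054)² / 0.007396 = 23.4, rounded up to 24 per arm, **48 in total**. 286/48 is about 6.

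**Could another formula rescue the stated inputs?** Total sample size under each variant:

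| Formula | 20% power, two-sided | 20% power, one-sided | 80% power, two-sided | 80% power, one-sided |
|---|---|---|---|---|
| Pooled | 48 | 26 | **286** | 226 |
| Pooled, continuity-corrected | 88 | 64 | 330 | 270 |
| Unpooled | 46 | 24 | 280 | 222 |
| Unpooled, continuity-corrected | 86 | 62 | 326 | 266 |
| Arcsine | 42 | 22 | 262 | 206 |

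At 20% power the largest total is 88. Among these variants only the two-sided, pooled, uncorrected formula at 80% power gives 286. A one-sided arcsine calculation at 90% power also happens to give 286, but it does not explain where the 20% comes from.

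**Power delivered at 3% versus 11.6%, two-sided 5%**

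| Per arm | Formula | Exact enumeration, uncorrected chi-square | Exact enumeration, Fisher's exact |
|---|---|---|---|
| 143 (N = 286) | 80.2% | 82.3% | 75.9% |
| 150 (N = 300) | 82.0% | 84.2% | 78.5% |

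The formula entry for 143 per arm is Φ[(0.086·√143 − 0.7211)/0.3628] = Φ(0.847) = 0.802. For 150 per arm it is Φ[(0.086·√150 − 0.7211)/0.3628] = Φ(0.916) = 0.820.

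**The case against.** The best reply is that this is a slip of labelling with no operational effect. The figures that govern the trial, 286 and 300, are right for 80% power. Any statistician will see that 20% is beta and recover the number from a textbook formula. A null result would in any case be read through the risk ratio and its 95% confidence interval, which the Statistical analysis section provides for, and not through the planned power. All of this stands, and it limits the consequence: the trial is not undersized, and a null result would still be interpretable. It does not make the sentence true. A reader can recover 286 only by overriding a stated input, and no other passage supplies the correct one.

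A second reply is that formula-level detail is often left to a statistical analysis plan, that a 5% threshold with 95% intervals points to two-sided testing, and that naming an uncorrected chi-square test back-fits a formula the investigators never stated. This has force. The absence of sidedness and test would not be a finding by itself, and the formula is inferred from the exact match, so the investigators should confirm it. Both details still belong in the corrected sentence because the power claim depends on them: at 143 per arm, Fisher's exact test has 75.9% power, not 80%. The protocol permits either test, but under the common rule based on expected cell counts the chi-square test would normally be used. The pooled rate of 0.073 gives 0.073 × 143 = 10.4 expected events in each arm.

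**Conclusion.** The concern holds. The stated power of 20% is wrong; the figure consistent with 286 participants is 80%, with 20% as the type II error. Taken literally, the stated inputs give 48 participants, about a six-fold mismatch, and no formula variant tried at 20% power exceeds 88.

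The error lies in a core design figure as documented, not in the size of the trial. The conclusion that 286 is adequate rests on the protocol's own rates of 3% and 11.6%, a two-sided 5% test and the uncorrected chi-square test. The 82.0% at 300 also requires that all 300 are analysed; the extra 14 were added to cover enrolment errors, so some may be lost.

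**What to change.** Reword the sentence in Sample size estimation along these lines: with expected rates of 3% and 11.6%, a two-sided alpha of 5%, power of 80% (beta 20%), 1:1 allocation and a Pearson chi-square test without continuity correction, 143 participants per arm (286 in total) are required. Add that recruiting 300 gives about 82% power by the same formula if all are analysed.

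Before adopting this, the investigators should confirm from their own calculation that this was the formula and sidedness used. If they used something else, they should state that instead; the correction of power to 80% (or of the label to beta) should be made once that calculation bears it out.

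The cost is one sentence in the protocol. The sample size, recruitment target, randomisation, outcomes and conduct are unchanged.

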**Statistical analysis**

Descriptive statistics will be conducted to describe data characteristics. Continuous data will be described with mean and standard deviation (SD) or median and interquartile range (IQR) depended on whether their distribution is normal or not. Categorical data will be described with percentage.

Comparison between groups will be performed by statistical test as follows: the chi-square or Fischer’s exact tests for categorical data (e.g. the outcome data), and the independent student t- or Mann-Whitney U tests for continuous data (normal and non-normal distribution, respectively). Risk ratios and their 95% confidence intervals, representing the strength of association between the factors of interest and the outcomes, will be estimated. A P-value of ≤ 0.05 will be considened as statistical significance.

Subgroup analysis will be conducted for naïve ampulla participants and participants who undergo high-risk procedures defined by pancreatic duct wiring, pancreatic duct injection, precut sphincterotomy, and balloon dilation of the ampulla.

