**Intervention**

Bolus fluid will be calculated to have a volume of 15 ml/kg of LRS. Then, 600 ml of this volume will be replaced with 50 ml of 20% human albumin^1,2^ and started ~ 1 h prior to procedure. The rest of the bolus fluid will be given subsequently. LRS will be administered at a rate of 3 ml/kg/h until 8 h post-ERCP, followed by the maintenance rate. Ideal body weight will be used in fluid calculation (for both intervention and control groups) if pariticipants weigh > 80 kg.

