**Control**

LRS will be administered at a fixed rate of 1.5 mL/kg/h and started approximately at 1 h before ERCP.

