**Co-interventions**

***ERCP procedure:***

ERCP will be performed under general anesthesia with prone or supine position depended on endoscopist preference. Steps of the procedure include selective bile duct cannulation, sphincterotomy, complete cholangiography, and therapeutic interventions regarding pathology. These steps can be modified and varied between cases as needed. Before termination, the rest of contrast media will be removed as much as possible. All participants will be discharged home after 24 h if uneventful.

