**Blinding**

Participants and outcome assessors will be blinded to the treatment allocation. Also, physician team, except endoscopists, will be blinded. Physician team will be unblinded in case a knowledge of treatment allocation is necessary, for example, PEP.

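### The high-risk-procedure subgroup is defined by what an unblinded endoscopist does after randomisation, so randomisation does not protect its risk ratio

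*Protocol*

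**What the plan says.** The protocol names two subgroups under Statistical analysis. The first rests on the state of the papilla: "Subgroup analysis will be conducted for naïve ampulla participants". The second rests on what is done at the procedure: "participants who undergo high-risk procedures defined by pancreatic duct wiring, pancreatic duct injection, precut sphincterotomy, and balloon dilation of the ampulla".

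Four other sections set the order of events and who knows the arm:

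- **Randomisation and concealment:** the allocation envelopes are those "which will be revealed during admission at 1 day before ERCP".
- **Intervention and Control:** the albumin-arm bolus is "started ~ 1 h prior to procedure", and the control infusion is "started approximately at 1 h before ERCP".
- **Blinding:** "Also, physician team, except endoscopists, will be blinded".
- **Co-interventions, ERCP procedure:** after listing the usual steps, the text adds "These steps can be modified and varied between cases as needed".

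The Statistical analysis section gives risk ratios with 95% confidence intervals as the effect measure. It does not mark the second subgroup as different in kind from the first.

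**The concern.** A subgroup comparison keeps the benefit of randomisation when membership is settled before allocation, or at least cannot be influenced by it. Here membership is settled during the ERCP, by an operator from whom the arm is not concealed and who has discretion over the steps. If that operator uses, or avoids, these manoeuvres more readily because of the fluid regimen, the two arms of the subgroup contain different kinds of patient. Their pancreatitis rates could then differ without any treatment effect, or a real effect could be masked.

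What is at stake is the reading of this one secondary result. A reader is likely to look to patients at higher procedural risk for a benefit of a preventive regimen, and would take a risk ratio there as randomised evidence. The protocol does not plan to show how often the manoeuvres were used in each arm, so the reader would have no direct sign of selection.

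**Working it through.** The protocol gives no figure for this subgroup, so there is nothing to reproduce. Its sample size concerns the overall comparison and does not enter the argument.

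**Step 1. Order of events, from the protocol**

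| Time | Event | Section |
|---|---|---|
| 1 day before ERCP | Allocation revealed | Randomisation and concealment |
| About 1 h before ERCP | Infusion starts in both arms | Intervention; Control |
| During ERCP | Operator, not blinded, varies steps as the case requires | Blinding; ERCP procedure |
| During ERCP | Manoeuvres that define the subgroup take place | Statistical analysis |

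Membership comes last. It is a post-randomisation variable, recorded after treatment has begun. Naïve ampulla, in its ordinary meaning, describes the papilla before the procedure, so the same objection does not reach it.

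**Step 2. How large could the distortion be?** All inputs in this step are assumed; none comes from the protocol. There is no treatment effect.

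- 30% of patients are difficult cases with a pancreatitis risk of 20%; 70% are easy cases with a risk of 5%. These shares and risks are the same in both arms.
- The manoeuvres are used in 80% of difficult cases in both arms.
- They are used in 15% of easy control cases and in a proportion e of easy albumin-arm cases.

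Share of an arm in the subgroup = 0.3 × 0.8 + 0.7 × e = 0.24 + 0.7e.

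Events in the subgroup, per patient randomised = 0.24 × 0.20 + 0.7e × 0.05 = 0.048 + 0.035e.

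Subgroup risk = (0.048 + 0.035e) / (0.24 + 0.7e).

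Control (e = 0.15): 0.05325 / 0.345 = 15.4%.

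| e in albumin arm | Subgroup risk, albumin arm | Risk ratio against control |
|---|---|---|
| 5% | 0.04975 / 0.275 = 18.1% | 1.17 |
| 10% | 0.0515 / 0.310 = 16.6% | 1.08 |
| 15% | 0.05325 / 0.345 = 15.4% | 1.00 |
| 20% | 0.0550 / 0.380 = 14.5% | 0.94 |
| 25% | 0.05675 / 0.415 = 13.7% | 0.89 |
| 30% | 0.0585 / 0.450 = 13.0% | 0.84 |
| 35% | 0.06025 / 0.485 = 12.4% | 0.80 |

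The row e = 15% shows that the bias vanishes when use does not depend on the arm. The first two rows show that it can run the other way.

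**Step 3. The same point in counts** (again assumed, no treatment effect). Control has 60 of 150 patients in the subgroup at 12% risk. The albumin arm has 60 such patients plus 15 easier ones at 4%. Its subgroup rate is (60 × 0.12 + 15 × 0.04) / 75 = 7.8 / 75 = 10.4%, and 10.4 / 12 = 0.87.

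**Step 4. The primary comparison.** Under the Step 2 inputs, the risk over all randomised patients is 0.3 × 0.20 + 0.7 × 0.05 = 9.5% in each arm, whatever the value of e. The distortion arises only from restricting the analysis to the subgroup.

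**The case against.** The strongest reply is that nothing in the protocol says endoscopists choose these manoeuvres by fluid arm. The discretion in the ERCP procedure section is tied to the needs of the case and to pathology, which are the same in expectation in both arms. The protocol exempts endoscopists from blinding but does not say that they act on the allocation. All of this stands. A reader might infer that the subgroup result will be biased; the documents support only that it is unprotected against bias.

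A second reply is that the illustrations are invented and modest. This too stands. In the scenario of Step 3, the chance of a chi-square P ≤ 0.05 is about 6.4%, against roughly 5% without selection, so that degree of selection would seldom create a significant result by itself. What remains is that the estimate is shifted by an unknown amount in an unknown direction, and that its confidence interval does not reflect this.

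A third reply is that the protocol makes no confirmatory claim for the subgroup: neither the objectives nor the sample size mention it. That is correct, and it limits the importance of the point. It does not remove it, because the protocol sets this subgroup beside naïve ampulla as though the two had equal standing.

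A reader might also go further and infer that no interaction test will be done, that the complementary groups will not be reported, or that multiplicity and low subgroup power are defects. The protocol does not support this. It is silent on the first three, which are commonly left to a statistical analysis plan that is not at hand, and it claims no power for any subgroup.

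**Conclusion.** The point holds in a limited form. The high-risk-procedure subgroup is formed after randomisation and after the infusion has started, by operators exempt from blinding, so its risk ratio should not be read as a randomised comparison. This follows from the protocol's own text and rests on no assumed number.

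The size of any bias cannot be stated. It is zero if use of the manoeuvres is independent of the arm. Under the assumed inputs above, and no treatment effect, the risk ratio runs from 1.00 down to about 0.80 when easier patients are added in the albumin arm, and rises above 1 when selection is reversed.

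The primary analysis does not depend on subgroup membership and is unaffected, as is the naïve-ampulla subgroup. This is an inexpensive improvement to a secondary analysis, not a flaw in the trial's main conclusion.

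**What to change.** Amend the subgroup paragraph under Statistical analysis in three ways:

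1. Report the frequency of each of the four high-risk manoeuvres by arm. A difference would suggest that membership depended on the arm. Similar frequencies would be reassuring but not proof, because the kind of patient selected can differ at equal frequency.
2. Label any risk ratio within the high-risk-procedure group exploratory and non-randomised, and attach no significance claim to it.
3. Keep naïve ampulla as the pre-specified subgroup analysis.

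The cost is a few lines of text and one table. No new data are needed, since the manoeuvres must already be recorded to form the subgroup, and recruitment, treatment and the primary analysis do not change. The one real downside is that the high-risk-procedure result is demoted to exploratory.

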**Monitoring and safety**

Any adverse events and protocol violation will be reported to the principal researcher. Appropriate treatments will be delivered to participants regarding their condition without delayed. Blinded allocation will be revealed if knowing of allocated intervention is important.

**Ethics**

This study will be conducted following the Declaration of Helsinki, the Belmont Report, and Godd Clinical Practice (GCP) guideline. The Institutional Review Board (IRB) of the Faculty of Medicine Vajira Hospital has approved this study (COA237/2564) before the first participant enrolment.

**Dissemination**

Results from this study will be disseminated via a peer-reviewed journal. No data that can identify individual participants will appear in the manuscript.

